#### Primary Outcome Analysis

Analysis of the sole primary outcome is focused on the difference in MoCA scores at week 8 between the combined intervention group and the routine care group. We will use ANCOVA for this comparison, adjusting for the baseline MoCA score as a covariate, to derive the primary efficacy conclusion (significance level set at *P*<.05).

#### Secondary and Exploratory Analysis

All secondary outcomes (eg, Fried Frailty Phenotype, Barthel Index, and 36-item Short Form Health Survey), as well as all pairwise comparisons between the 4 intervention groups, will be considered exploratory analyses. Continuous variables will be tested for normality using the Shapiro-Wilk test. Normally distributed variables will be compared using 1-way ANOVA, followed by the Bonferroni correction for post hoc comparisons. Non-normally distributed variables will be analyzed using the Kruskal-Wallis test, followed by the Dunn test for pairwise comparisons. For changes over multiple time points (weeks 0, 6, 8, and 12), repeated measures ANOVA or the Friedman test (for nonnormal data) will be used for within-group and between-group comparisons over time. The categorical variables (eg, frailty status) will be analyzed using chi-square tests or the Fisher exact test.

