##### Evaluation Time Points

All outcome measures will be assessed at the following time points: baseline (week 0), midintervention (week 6), postintervention (week 8), and follow-up (week 12).

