#### Strategy for Controlling Multiple Comparison Risk

To strictly control the risk of type I error inflation due to multiple comparisons, this study will only perform statistical inference and power evaluation on the primary outcome comparison. Formal multiple comparison adjustments will not be applied to the secondary outcomes or multitime-point comparisons. These results will be considered exploratory findings, used only to describe trends and generate future research hypotheses, and will be interpreted with extreme caution, not as definitive conclusions.

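### A Shapiro-Wilk test on the trial data chooses between mean-based and rank-based tests for each continuous secondary outcome, so the compared quantity is not fixed in advance and baseline is not adjusted for (exploratory analyses only)

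*Protocol article*

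**What the plan says.** The rule is in the protocol article, Secondary and Exploratory Analysis. It opens with "Continuous variables will be tested for normality using the Shapiro-Wilk test" and then branches:

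- If the variable passes: "Normally distributed variables will be compared using 1-way ANOVA, followed by the Bonferroni correction for post hoc comparisons".
- If it fails: "Non-normally distributed variables will be analyzed using the Kruskal-Wallis test, followed by the Dunn test for pairwise comparisons".
- Over time: "repeated measures ANOVA or the Friedman test (for nonnormal data) will be used for within-group and between-group comparisons over time".

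No single method is named for any continuous secondary outcome. The article does not give the level of the pretest, or say whether it is run by arm, pooled over arms, once or at each visit, or on residuals. Assessments are at weeks 0, 6, 8 and 12.

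Three statements limit the reach of the rule. Primary Outcome Analysis fixes the MoCA comparison: "We will use ANCOVA for this comparison, adjusting for the baseline MoCA score as a covariate". The secondary outcomes, "as well as all pairwise comparisons between the 4 intervention groups, will be considered exploratory analyses". Strategy for Controlling Multiple Comparison Risk adds: "Formal multiple comparison adjustments will not be applied to the secondary outcomes or multitime-point comparisons".

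**The concern.** ANOVA compares means; Kruskal-Wallis and Dunn compare rank distributions. When a preliminary test on the same data chooses between them, the quantity reported for an outcome is known only after the data are in. Shapiro-Wilk is also a poor guide to whether ANOVA is valid here. With bounded, discrete scales (Fried 0-5, GDS-15 0-15, Barthel 0-100) it reacts to discreteness, ceiling and sample size.

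Neither branch uses baseline as a covariate. Repeated measures ANOVA includes week 0 only as one of the visits. The article does adjust for baseline in the MoCA analysis, and it collects baseline for every other outcome.

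At stake is the usefulness of the secondary results. The article wants them to describe trends and suggest hypotheses. That needs an effect estimate with an interval, on the same footing at each visit and as precise as the data allow. A P value from whichever test was selected does not supply this.

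**Working it through.** The plan gives no figure for this rule, so there is none to reproduce. The checks below take 39 per arm and four arms from Sample Size Calculation and the visits from Evaluation Time Points. Assumptions: pretest level 0.05, visit correlation 0.6, and the distribution shapes named.

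**1. Type I error.** Null simulation, 4 arms of 39, 4,000 replicates, Shapiro-Wilk in each arm; ANOVA if all four arms pass, otherwise Kruskal-Wallis.

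| Shape (assumed) | All arms pass | Two-step rule | ANOVA always | Kruskal-Wallis always |
|---|---|---|---|---|
| Normal | 81% | 4.9% | 4.4% | 4.7% |
| Binomial, 0-15 scale | 10% | 4.4% | 4.4% | 4.4% |
| 0-100 in steps of 5, ceiling | 0% | 4.6% | 4.8% | 4.6% |
| Gamma, shape 4 | 3% | 4.8% | 5.0% | 4.6% |
| Gamma, shape 10 | 31% | 5.3% | 5.5% | 5.0% |

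The two-step rule stays near 5%, and so does either test fixed in advance. The pretest protects nothing that a fixed choice would lose.

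**2. Switching between visits, if the pretest is repeated at each visit.** Let p be the chance of passing at one visit. If the three visits were independent, the chance that the method differs among weeks 6, 8 and 12 would be 1 − p³ − (1 − p)³.

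- Normal data, one pooled test: p = 0.95, giving 1 − 0.8574 − 0.0001 = 0.14.
- Normal data, four arms must pass: p = 0.95⁴ = 0.8145, giving 1 − 0.5404 − 0.0064 = 0.45.

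Simulation with correlation 0.6 (2,000 replicates, same distribution at every visit) gave 14% pooled and 44% by arm. With mild skew (lognormal, log-scale SD 0.15) it gave 66% pooled and 69% by arm.

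**3. Scales that always fail.** The ceiling-limited score passed in 0% of trials, so its method would not switch: it would always get the rank test. The inclusion criteria admit only Fried scores of 1 or 2, so the week 0 Fried score has two values and must fail (largest possible P about 1e-8 at n = 39). Switching and permanent diversion to ranks are therefore different consequences and fall on different outcomes.

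**4. Cost of leaving out baseline.** Take two arms of 39, an assumed effect of 0.6 SD and correlation 0.6 with baseline.

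- Unadjusted: noncentrality 0.6 × √(39/2) = 2.65, power 74%.
- ANCOVA: residual SD factor √(1 − 0.6²) = 0.8, so 0.6/0.8 = 0.75; noncentrality 0.75 × √(39/2) = 3.31, power about 90%.

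**The case against.** The strongest reply is that little depends on this rule. The primary comparison is a fixed ANCOVA, the factorial interaction is also placed in ANCOVA, and everything the pretest touches is labelled exploratory with inference disclaimed. Frailty status, including the move from prefrail to nonfrail on which the Fried section focuses, is analysed as categorical and never meets Shapiro-Wilk. All of this stands and limits the weight.

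A reader might infer that the pretest inflates type I error. The check does not support that: overall error stays at 4.4% to 5.3%. Some error rates within a selected branch drift from 5%, for example 6.3% for Kruskal-Wallis after a failed pretest on normal data, but the overall rate does not.

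A reader might also infer that the plan prescribes a change of method between visits. It does not. It classifies variables without saying that the test is repeated at each visit, and its longitudinal analysis names one method spanning the visits. How the test is applied may be settled in an analysis plan not shown here. Visit switching is a possibility that the text leaves open.

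Nor do the documents show that most scales would go to rank tests, since every distribution shape used here is assumed. What survives is the stated rule itself: the choice between means and ranks is conditional on the data, and baseline is not a covariate in either branch.

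**Conclusion.** The point holds as a minor to moderate weakness confined to the exploratory analyses. The compared quantity for each continuous secondary outcome depends on a normality test in the trial data, and the collected baseline is not used for adjustment. The pretest neither inflates overall type I error nor adds protection.

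The switching rates of about 14% to 45% for normal data apply only if the test is repeated at each visit, and rest on a 0.05 pretest level and a visit correlation of 0.6. The higher rates rest on an assumed mild skew. The precision gain from baseline adjustment (74% to about 90% power in the example) rests on the same correlation and an assumed effect of 0.6 SD. The primary efficacy conclusion and the sample size are unaffected.

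**What to change.** Delete the Shapiro-Wilk rule and name one method per outcome, used at every visit whatever the data look like:

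- SF-36 component summaries, GDS-15, Barthel Index and TCM syndrome score: ANCOVA on the visit score, adjusted for that outcome's own baseline, reporting adjusted mean differences with robust confidence intervals.
- Fried score: one method suited to an ordinal score, fixed in advance, beside the planned categorical analysis of frailty status. Proportional odds is one reasonable choice among several.
- Kruskal-Wallis with Dunn: keep only as a labelled sensitivity analysis.

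This is a wording change, best made before any outcome data are seen. It needs no new data and no change in sample size. The cost is slightly more analysis work and reliance on robust intervals for the skewed scales.

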### Sample Size Calculation

This study uses the MoCA score as the sole primary outcome measure, focusing specifically on the change from baseline to week 8. The primary comparison of interest is the difference in therapeutic efficacy between the combined intervention group and the routine care group.

Based on previous literature concerning nonpharmacological TCM interventions for cardiovascular and cognitive conditions, we hypothesize that the improvement in MoCA scores in the combined intervention group after 8 weeks will exceed that of the routine care group by a clinically meaningful difference (△µ) of approximately 3 points. We acknowledge that the estimated effect size (standardized mean difference ≈0.7-0.9) cited in similar studies may appear optimistic. However, this anticipated 3-point improvement is supported by the moderate-to-strong effect trend consistently reported in meta-analyses of comparable TCM external therapies, justifying its use for the primary calculation.

Assuming an SD (σ) of approximately 4, a one-way ANOVA was used to estimate the required effective sample size. The significance level (α) was set at .05, and statistical power (1–β) at 0.80. The initial calculation indicated a required effective sample size of 33 participants per group.

Considering a potential dropout rate of 15%, the required number of participants to be recruited per group is calculated as approximately 33/(1‐0.15)=38.82. The final sample size was therefore rounded up to 39 participants per group to ensure adequate retention and statistical power, resulting in a total sample size of 156 participants.

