#### Mechanism Verification and Interaction Test

To formally explore whether the combined therapy offers a synergistic effect (superior to the simple sum of the individual therapies), we will conduct a formal interaction analysis using a 2×2 factorial structure (Du-moxibustion factor×spine-pinching factor) within the ANCOVA framework. Furthermore, preplanned contrast analyses will be performed to test specific hypotheses, including the superiority of the combined intervention group over the individual Du-moxibustion group and the individual spine-pinching group. These results will also be treated as exploratory findings.

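### On the nonnormal branch the Friedman test cannot give the planned between-arm comparison over time; secondary outcomes also lack baseline adjustment and a single multiplicity rule

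*Protocol article*

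**What the plan says.** All references are to the Protocol article.

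- **Primary outcome** (Primary Outcome Analysis): MoCA at week 8, combined versus routine care, by ANCOVA, "adjusting for the baseline MoCA score as a covariate".
- **Secondary outcomes, single comparison** (Secondary and Exploratory Analysis): "Normally distributed variables will be compared using 1-way ANOVA, followed by the Bonferroni correction for post hoc comparisons". If normality fails: "Non-normally distributed variables will be analyzed using the Kruskal-Wallis test, followed by the Dunn test for pairwise comparisons". No covariate is named on either branch.
- **Secondary outcomes over weeks 0, 6, 8 and 12** (same section): "repeated measures ANOVA or the Friedman test (for nonnormal data) will be used for within-group and between-group comparisons over time".
- **Visits** (Evaluation Time Points): every outcome is measured at those four weeks, so each secondary outcome has a baseline value.
- **Multiplicity** (Strategy for Controlling Multiple Comparison Risk): "Formal multiple comparison adjustments will not be applied to the secondary outcomes or multitime-point comparisons". The results concerned are to be "used only to describe trends and generate future research hypotheses".
- **Other use of ANCOVA** (Mechanism Verification and Interaction Test): the 2×2 interaction is tested "within the ANCOVA framework", with neither outcome nor covariate named.

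**The concern.** There are three separate problems, in falling order of weight.

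1. **The Friedman test is given a task it cannot do.** It is a one-sample test of whether visits differ within participants. If the arms are pooled, it tests the average time trend. If it is run arm by arm, it gives four within-arm P values and no comparison between them. This branch is likely to be used, because several secondary scales are bounded (Fried 0 to 5, GDS-15 0 to 15, Barthel 0 to 100). In older adults who are tested four times and all receive routine care, a shared change over time is plausible, and the planned test could present it as a treatment result.
2. **Baseline is used for MoCA but not named for anything else.** This costs precision, not validity.
3. **Two statements on multiplicity do not fit together as written.** One section corrects the post hoc comparisons, and a later one says that secondary outcomes receive no formal adjustment. An analyst could follow either.

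**Working it through.** The plan gives no figure of its own on this point. The sample size figure of 33 evaluable participants per arm is used below only as an input.

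**Inputs from the Protocol article:** 4 arms; 33 evaluable per arm (Sample Size Calculation); 4 visits; "The significance level (α) was set at .05" (sidedness is not stated, so two-sided is assumed). **Assumed:** the within-participant correlation between visits (0.6 in the simulation) and the baseline to follow-up correlation r (0.3 to 0.7). The documents give neither.

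**Step 1: what Friedman tests.** Simulation with 4 arms × 33 participants × 4 visits and 1,000 runs; shifts apply at weeks 6, 8 and 12.

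| Truth | Pooled Friedman rejects | Friedman within each arm rejects |
|---|---|---|
| No change, no arm difference | 5.2% | 3.9% to 5.4% |
| Common 0.5 SD gain, no arm difference | 100% | 79% to 80% |
| Arm shifts −0.375, 0, 0, +0.375 SD, no average trend | 4.3% | 53.0%, 4.9%, 5.3%, 54.7% |

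In the second row the arms are identical and the pooled test always rejects. In the third row the arms differ and it rejects at its null rate. The shifts there were chosen to cancel on average, to show that the pooled test responds to the average trend and not to the arm contrast.

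Running the test in each arm and comparing verdicts does not rescue it. In the second row, two arms with the same true gain would disagree on significance with probability of about 2 × 0.80 × 0.20 = 0.32.

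The simulated data are normal, but the result follows from the structure of the test: its ranks are formed within participants, and arm does not enter.

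**Step 2: precision lost without baseline adjustment.** Relative variance of an arm contrast at one visit:

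- follow-up scores: 1
- change scores: 2(1 − r), for equal variances at baseline and follow-up
- ANCOVA: 1 − r²

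The ANCOVA saving is therefore r² against follow-up scores, and 1 − (1 + r)/2 against change scores.

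| r (assumed) | ANCOVA factor, 1 − r² | Saving v follow-up scores | Participants needed without adjustment, 1/(1 − r²) | Saving v change scores |
|---|---|---|---|---|
| 0.3 | 0.91 | 9% | 1.10 times | 35% |
| 0.5 | 0.75 | 25% | 1.33 times | 25% |
| 0.7 | 0.51 | 49% | 1.96 times | 15% |

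These factors apply to the ANOVA branch, not exactly to rank tests. For the Fried score, entry is restricted to 1 or 2 points at baseline, so r is probably at the low end.

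**Step 3: the two multiplicity statements.** Four arms give 4 × 3 / 2 = 6 pairwise contrasts per outcome. The threshold is 0.05 without correction and 0.05/6 = 0.0083 with Bonferroni. By simulation (33 per arm, 20,000 runs, no true differences), the chance of at least one false positive within one outcome is about 0.20 without correction and about 0.04 with it.

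**The case against.** The best case for the plan has four parts.

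- **Arms can still be compared.** This stands. Kruskal-Wallis with Dunn compares arms at any single visit on the nonnormal branch, and repeated measures ANOVA supplies a group-by-time test on the normal branch. A reader might infer that between-arm results for skewed scales are unobtainable altogether. The text does not support that: only the longitudinal between-arm comparison on the nonnormal branch is missing.
- **Week 0 in the repeated measures ANOVA does no harm.** This stands too. A reader might infer that counting week 0 as an outcome level dilutes the arm effect. That would apply to an arm main effect averaged over all visits, which the plan never names as its test. The method is introduced for changes over time, so the relevant term is group-by-time, and week 0 does not dilute that term.
- **Unadjusted tests are valid, and covariates for exploratory outcomes may sit in an analysis plan that is not shown.** This stands in part. The text also leaves open whether the one-way ANOVA uses visit scores or changes from baseline. The lack of adjustment is therefore a missed and nearly free gain, not an error.
- **The two multiplicity statements may concern different families**, Bonferroni within an outcome and none across outcomes or visits. That reading is reasonable, but the article does not state it. A reader might infer a flat contradiction that obliges the sponsor to delete Bonferroni. The documents support only that the sections must be reconciled. Nor can the practical cost be measured with the 3-point, SD 4 assumption, which was made for MoCA in combined versus routine care and not for the secondary outcomes.

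None of this answers the Friedman point. Exploratory status does not make a test without a group term into a between-group test.

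**Conclusion.** The Friedman assignment is wrong as written. For nonnormal secondary outcomes the planned between-arm comparison of change cannot be produced, and a shared time trend could be misread as a treatment effect. This follows from the structure of the test; the simulated rates illustrate it under an assumed correlation of 0.6.

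The absence of a named baseline adjustment costs precision only. Against follow-up scores the variance saving forgone is about 9% to 49% for r from 0.3 to 0.7, and that range is an assumption.

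The multiplicity wording is unclear rather than irreconcilable. For one outcome it leaves open a familywise error anywhere between about 0.04 and about 0.20.

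All affected analyses are labelled exploratory and the primary MoCA ANCOVA is untouched. The section should be corrected, but the trial's main conclusion does not depend on it.

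**What to change.** 1. Remove the Friedman test as a between-group method. If it is kept, limit it to describing change within an arm, and do not compare its P values across arms.
2. Compare arms on each continuous secondary outcome with baseline-adjusted ANCOVA at each visit, or with one mixed model over weeks 6, 8 and 12 containing the outcome's own baseline value, arm, visit and arm-by-visit. Where residuals are skewed, use robust or bootstrap intervals. Frailty status can stay with the categorical methods already named.
3. State one multiplicity rule in both sections. Examples are Bonferroni for the six pairwise contrasts within an outcome and nothing across outcomes or visits, or no adjustment at all with estimates and 95% confidence intervals.

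The cost is wording and slightly more modelling. No new data are needed, since week 0 values are already scheduled. If the mixed model is chosen, the text should also say whether values filled in by last observation carried forward (Statistical Analysis, Overview) enter it.

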#### Mechanism Verification and Interaction Test

To formally explore whether the combined therapy offers a synergistic effect (superior to the simple sum of the individual therapies), we will conduct a formal interaction analysis using a 2×2 factorial structure (Du-moxibustion factor×spine-pinching factor) within the ANCOVA framework. Furthermore, preplanned contrast analyses will be performed to test specific hypotheses, including the superiority of the combined intervention group over the individual Du-moxibustion group and the individual spine-pinching group. These results will also be treated as exploratory findings.

#### Strategy for Controlling Multiple Comparison Risk

To strictly control the risk of type I error inflation due to multiple comparisons, this study will only perform statistical inference and power evaluation on the primary outcome comparison. Formal multiple comparison adjustments will not be applied to the secondary outcomes or multitime-point comparisons. These results will be considered exploratory findings, used only to describe trends and generate future research hypotheses, and will be interpreted with extreme caution, not as definitive conclusions.

### Safety Monitoring

Adverse events will be monitored and recorded after each intervention session, including moxibustion burns, skin allergies, moxibustion syncope, and localized tenderness in the intervention groups, as well as psychological or emotional discomfort (eg, anxiety) in the control group. Adverse events will be classified by severity: mild (no treatment required), moderate (intervention paused; eg, cold compress for burns), and severe (intervention terminated and referral required; eg, hospitalization). The research nurse will document the time, symptoms, management, and outcomes in the CRF. Serious adverse events, such as hospitalization or life-threatening conditions, will be reported to the ethics committee within 24 hours. The DSMC will oversee trial safety and may trigger unblinding if necessary. Monitoring will cover the 8-week intervention and 12-week follow-up periods.

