### Routine Care Group

Participants in the control group will receive 30-minute health education sessions twice per week, conducted by registered nurses in classrooms or consultation rooms. Education will be delivered using Microsoft PowerPoint presentations, video demonstrations, and interactive Q&A sessions. Printed health education manuals will also be provided. The curriculum includes:

Dietary guidance: low-salt, low-fat diet with balanced nutrition (eg, omega-3-rich fish, fruits, and vegetables);Exercise advice: moderate aerobic exercise (eg, 30 min of brisk walking or Tai Chi daily);Cognitive health strategies: memory training techniques (eg, associative memory and number games) and psychological health management.Frequency and duration: twice per week for 8 consecutive weeks (total of 16 sessions).Safety: any psychological or emotional discomfort (eg, anxiety) reported after sessions will be recorded. No invasive procedures are involved.

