### Spine-Pinching Group

Details pertaining to the participants in the spine-pinching group are as follows:

Position: the position should be prone, with the back exposed.Method: starting from the sacrococcygeal region along the midline of the spine, pinch the skin and move upward toward the seventh cervical vertebra. The procedure is performed along 3 lines centered on the spine (left bladder meridian, right bladder meridian, and Du meridian). For each line, perform 3 pinches, followed by lifting (pinch 3 times and lift once) for 4 to 5 cycles. Acupressure is applied to the Xinshu (HT7), Shenshu (KI3), Pishu (SP3), Weishu (ST25), Ganshu (LV3), and Sanjiaoshu (SJ5) points (1 min per acupoint). The acupoint locations are shown in Figure 2, and the manipulation technique is illustrated in Figure 3. The total treatment duration is 15 to 20 minutes.Frequency and duration: the frequency is twice per week for 8 weeks, totaling 16 sessions.Safety: after each intervention, skin tenderness or muscle discomfort will be monitored and recorded in the CRF.

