### Quality Control

Before the trial begins, all personnel, including operators, assessors, and data entry staff, will receive training on moxibustion and spinal pinching techniques, safety precautions, and the 8-week treatment schedule (1 session/wk for control group; 2 sessions/wk for intervention groups). Standardized assessments of MoCA and Fried frailty scores, as well as questionnaire distribution and verification, will be covered through both theoretical and practical sessions. Randomization and blinding protocols outlined in the “Randomization, Allocation, and Blinding” section will be followed. A noninvestigator will generate the randomization sequence using SAS 9.3 and perform allocation concealment. Participants will be unaware of their group assignments or intervention types. Although operators will not be blinded, they will not participate in assessments. A pilot study with 4 prefrail older participants will be conducted to refine the procedures (eg, frequency and technical steps). Data collection will avoid suggestive language, and questionnaires will be reviewed on-site. Double-checking by 2 personnel will ensure data quality. The DSMC and ethics committee will oversee trial quality through regular audits.

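### Non-serious adverse events are named arm by arm and graded by the action taken, so their rates and grades may not be comparable between arms

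*Protocol article*

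**What the plan says.** **Events named by arm.** Safety Monitoring names two sets of events to be watched for. For the active arms the set is "including moxibustion burns, skin allergies, moxibustion syncope, and localized tenderness in the intervention groups". For routine care the same sentence then adds a different one: "as well as psychological or emotional discomfort (eg, anxiety) in the control group". The arm descriptions follow the same pattern:

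- Routine Care Group: "any psychological or emotional discomfort (eg, anxiety) reported after sessions will be recorded".
- Du-Moxibustion Group: skin reactions such as redness and burns.
- Spine-Pinching Group: "skin tenderness or muscle discomfort will be monitored and recorded in the CRF".
- Combined Intervention Group: redness, burns or tenderness of the skin.

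**Timing.** "Adverse events will be monitored and recorded after each intervention session". Table 1 also ticks adverse-event monitoring at weeks 0, 6, 8 and 12, without a split by arm.

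**Severity.** Mild means that no treatment was needed. The other two grades are "moderate (intervention paused; eg, cold compress for burns), and severe (intervention terminated and referral required; eg, hospitalization".

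**Session frequency in control.** Quality Control has "1 session/wk for control group; 2 sessions/wk for intervention groups", and Study Design also has control attending once a week. The Routine Care Group section and Table 1 have control attending twice a week.

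**Objective.** The abstract's objective names safety alongside efficacy.

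**The concern.** Counts of adverse events by arm will be read as a comparison, even if no test is attached to them. The comparison is sound only if the same events are asked about in the same way, equally often, and graded on a scale that means the same thing in each arm. The article's wording departs from this on content and on grading, and possibly on frequency.

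The events at risk are the non-serious ones that are not tied to a procedure: emotional discomfort, fainting, muscle or back tenderness. If staff follow the named lists, emotional discomfort will be looked for mainly in control, and musculoskeletal complaints mainly in the spine-pinching arm. An event that nobody asked about cannot be recovered at analysis.

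**Working it through.** The documents state no adverse-event figure, so there is none to reproduce. The check is a comparison of sections, followed by an illustration with assumed rates.

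**1. Named events.** Emotional discomfort is named only for control. Yet Ethical Considerations lists burns and emotional distress as study risks without assigning either to an arm, and Intervention Methods gives routine care to everyone. Muscle discomfort is named for spine-pinching but not for the combined arm, although the combined arm receives the same pinching procedure. The mismatch therefore also touches combination versus component, not only active versus control.

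**2. Severity scale, applied to cases.**

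| Case | Grade under the stated scale |
|---|---|
| Redness, nothing done | Mild |
| Burn given a cold compress, sessions continue | Not mild, because treated. The moderate criterion (a pause) is not met, although a cold compress is the example given for that grade |
| Intervention ended, no referral | Only half of the severe criterion is met |
| Hospitalization | The example for severe, and also an example of a serious adverse event |
| Same anxiety in control and in a moxibustion arm | Depends on whether a class or a heat treatment is paused |

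The second case is foreseen by the article itself: the Du-Moxibustion and Combined Intervention sections offer a cold compress or a suspension as alternatives. In the last case the grade follows a decision about the intervention, and the Blinding section says that practitioners cannot be blinded.

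**3. Illustration of unequal capture.** Observed risk = true risk × share captured. Assume the same true risk in all arms, full capture in control and a share c in an active arm. The observed control-to-active ratio is then 1/c:

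- c = 75%: 1/0.75 = 1.33
- c = 50%: 1/0.50 = 2.0
- c = 25%: 1/0.25 = 4.0
- c = 100%: 1.0, no distortion

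At an assumed true risk of 20%, the false differences are 20% − 15% = 5 points, 20% − 10% = 10 points and 20% − 5% = 15 points. With 39 per arm and c = 50%, about 39 × 0.20 = 7.8 participants would be recorded in control and 39 × 0.10 = 3.9 in one active arm.

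**4. Number of recording occasions.** Twice a week for 8 weeks is 16 occasions and once a week is 8. The active arms have 16. Control has 8 under Study Design and Quality Control, and 16 under Routine Care Group and Table 1. With a fixed chance q of recording at each occasion (assumed), the chance of at least one record is 1 − (1 − q)^k:

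| q | k = 8 | k = 16 |
|---|---|---|
| 1% | 7.7% | 14.9% |
| 2% | 14.9% | 27.6% |
| 5% | 33.7% | 56.0% |

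The k = 8 column applies to control only if once weekly is the plan. Under twice weekly all arms sit in the k = 16 column and session count creates no difference.

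**The case against.** The case against a stronger claim is good, and much of it stands.

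- *The lists are open.* Safety Monitoring introduces its events as inclusions, and no section says that other events go unrecorded. Burns from moxa cannot occur in control, so some difference in naming is natural. This stands: the text creates a risk of unequal capture but does not prescribe it.
- *Common visits exist.* Table 1 schedules monitoring at the same visits in all arms, and serious events follow one rule. This stands. However, Table 1 states no common content for those visits.
- *Mood is measured in every arm* through the GDS-15 and the SF-36 mental component. True, but these are outcome scores, not adverse-event records.
- *No between-arm safety test is described*, and formal inference is limited to the primary comparison. True, so the comparison affected is an implied, descriptive one.
- *Symptoms and management go into the CRF alongside the grade*, so events could be regraded. This softens the grading point for events that were recorded, but does nothing for those never asked about.
- *This is a condensed article and the CRF is not shown.* A common adverse-event page may exist. The point therefore rests on what the article states, not on what it leaves out.

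A reader might infer that the safety comparison is biased by design, that every background symptom would show up more often in the active arms, or that 8 against 16 occasions produces a ratio of 27.6/14.9 = 1.85. The documents support none of these. The ratio takes the once-weekly sections and ignores the two places that say twice weekly. Even under once weekly it needs a fixed chance per occasion: if each query captured everything since the last one, fewer queries need not mean fewer records. And naming emotional discomfort only for control would push that event the other way.

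**Conclusion.** The point holds as a risk to comparability for non-serious adverse events. Two facts are firm: the named events differ by arm in Safety Monitoring and in the four arm descriptions, and all three severity grades are defined by action. The gaps in the scale are firm too, and do not depend on whether the event lists are open. Grading is thus the stronger half of the point.

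The size is unknown. The ratios of 1.33 to 4.0 rest on assumed capture shares of 75% to 25% in an active arm and full capture in control. Unequal ascertainment from session frequency is conditional: it arises only if control attends once weekly, and the four places that state the frequency must be reconciled. Serious adverse events and the primary efficacy analysis are not affected. Because safety is a stated objective and uncollected events cannot be recovered, the change should be made before enrolment.

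**What to change.** 1. Use one adverse-event checklist in all four arms, covering skin, musculoskeletal, fainting, psychological and other events, plus one open question.
2. Ask it at the same fixed times in every arm, for example weekly, and at the week 6, 8 and 12 visits already in Table 1. Observation after each session can continue in addition, flagged as such so that it can be separated at analysis.
3. Grade severity by the event's symptoms and functional impact. Record action taken and seriousness in separate fields, so that severe and serious are no longer merged through the hospitalization example.
4. Reconcile the control session frequency across Study Design, Routine Care Group, Table 1 and Quality Control.

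None of this alters any rule for pausing or ending treatment. The cost is one extra CRF page and a short regular query, felt mainly in control if it turns out to have fewer sessions.
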